### Data analysis

Data will be entered and analyzed using SPSS version 13. Each participant will have a registration number. All printed questionnaires and datasets will be stored in a secure locker and computer, respectively. Missing data will be handled by random coefficient analysis [68]. Intention-to-treat analysis will be performed for dropout participants during treatment sessions or follow-up assessments. Dropout participants will not be excluded from the sample size and data analysis. There will be no planned interim analyses and no planned stopping rules for this trial. The mean (standard deviation) or median (inter-quartile range) will be calculated for quantitative variables. For categorical variables, frequency (percentages) will be used. To check the normality of data, Shapiro-Wilk, graphical methods, and numerical indices will be used.

Quantitative demographic variables between the three groups will be compared using one-way ANOVA or Kruskal-Wallis tests. Chi-squared will be used for comparing the categorical variables between the groups. If there will be no significant difference between various outcome measures in the three groups at baseline, outcome measures will be analyzed using a 3 × 5 repeated measure analysis of variance with group (occupation-based interventions with responsibility feedback; occupation-based interventions without responsibility feedback; conventional) as between-subject factor and time (baseline, session 9, session 17, post-intervention, follow-up) as within-subject factor. A Tukey post hoc test will be performed for multiple comparisons. However, if a significant difference will be obtained for outcome measures in the three groups at baseline, a separate regression analysis will be done by considering group and baseline as covariates at each assessment point (i.e., session 9, session 17, post-intervention (week 13), follow-up (week 25)). The differences will be calculated via Kruskal-Wallis. All analyses will be considered significant with a 2-tailed *P* < 0.05.

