### Sample size calculation

The sample size was estimated using the G-Power software with Cohen’s *f* standardized effect size of 0.25, correlation among repeated measures of 0.25, power of 80%, and first type error of 5% based on the primary outcome measure (i.e., Utrecht Scale for Evaluation of Rehabilitation-Participation Satisfaction) [49]. The total sample size was calculated as 39 subjects which increased to 45 subjects by assuming a 15% dropout rate. In order to assure the sufficiency of the sample size, power calculation will be performed again at the end of the trial.

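### The Data analysis section names two incompatible analyses of the same outcomes, and the ones said to give the results do not keep the dropouts that the section promises to keep

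*Protocol article*

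**What the plan says.** Everything at issue except the sample size stands in the Data analysis section of the protocol article.

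- **Population.** "Intention-to-treat analysis will be performed for dropout participants during treatment sessions or follow-up assessments", followed by "Dropout participants will not be excluded from the sample size and data analysis".
- **Missing data.** "Missing data will be handled by random coefficient analysis", with a literature reference and no further detail.
- **Outcome analysis, first branch.** The condition is "If there will be no significant difference between various outcome measures in the three groups at baseline". If it is met, "outcome measures will be analyzed using a 3 × 5 repeated measure analysis of variance with group" as the between-subject factor and the five assessments as the within-subject factor. Tukey comparisons follow.
- **Outcome analysis, second branch.** If the arms do differ at baseline, a separate regression is fitted at each of the four later assessments, with group and the baseline value as covariates. Kruskal-Wallis is also named for the differences.
- **Sample size calculation section.** "The total sample size was calculated as 39 subjects which increased to 45 subjects by assuming a 15% dropout rate".

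The article does not say how the random coefficient analysis relates to either branch.

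**The concern.** A classical repeated-measures ANOVA works on one row of five values per person, and a person with a gap in that row is left out. The article does not say this; it is a property of the method. The per-visit regressions and Kruskal-Wallis tests use only those seen at the visit in question. So neither stated branch, run as written, keeps every dropout.

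Random coefficient analysis does keep them, because it is a mixed model fitted to whatever visits were observed. For that reason it competes with the ANOVA and is not a preparatory step for it. If it is the analysis, the ANOVA and its baseline-dependent branching have no role. If the ANOVA is the analysis, the promise about dropouts fails.

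Two things are at stake. An analysis of complete cases can be biased when leaving depends on scores already observed, whereas a correctly specified mixed model remains valid under that weaker, missing-at-random condition. And with two eligible models for the primary outcome, the choice could be made after the data are seen.

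**Working it through.** **1. Which test the sample size belongs to.** Inputs from the Sample size calculation section: f = 0.25, correlation 0.25, alpha 0.05, power 80%. From Trial design and Data analysis: k = 3 groups, m = 5 assessments. Sphericity is assumed (epsilon = 1), because the article does not state it.

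For the group-by-time interaction:
- noncentrality λ = f² × N × m / (1 − ρ)
- df1 = (k − 1)(m − 1) = 8
- df2 = (N − k)(m − 1)

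At N = 39, λ = 0.0625 × 39 × 5 / 0.75 = 16.25 and df2 = 144, which gives power 0.812. The smallest N divisible by three that reaches 80% is 39, so the plan's figure is reproduced. With the same inputs the between-group effect would need 66 and the time effect 30. The stated size therefore matches the interaction test of the 3 × 5 ANOVA.

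**2. Dropout allowance.** 39 × 1.15 = 44.85, rounded to 45. Dividing instead, 39 / 0.85 = 45.9, or 46. The difference of one is immaterial here.

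**3. Who remains in the ANOVA.** 45 × 0.85 = 38.25, so about 38 complete and about 7 omitted, together with all the visits those 7 did attend.

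| N analysed | λ | df2 | Power (epsilon = 1) |
|---|---|---|---|
| 45 | 18.75 | 168 | 0.877 |
| 39 | 16.25 | 144 | 0.812 |
| 38 | 15.83 | 140 | 0.799 |

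At the plan's own dropout rate, power stays essentially at its target. If sphericity fails, power is lower at every N (at epsilon = 0.75: 0.717 for 39 and 0.702 for 38), but the step from 39 to 38 stays small.

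**4. Who remains in a mixed model.** Baseline data are taken before allocation (Randomization and blinding section), so every randomised participant has at least one value. In one simulated data set with 45 participants and 7 dropouts, 38 had complete data, giving 38 × 5 = 190 observations to the ANOVA. The mixed model used all 45 participants and 205 of the 225 possible observations.

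**5. How large a bias could be.** The documents give no dropout pattern, so this is an illustrative extreme. Suppose scores are normal, 15% of one arm leave after session 9, and those who leave are exactly the lowest scorers at that visit.
- The cut-off is z = −1.036, with normal density 0.233.
- The complete-case mean of that arm at session 9 shifts upward by 0.233 / 0.85 = 0.27 SD.
- At the plan's correlation of 0.25, its mean at each other visit shifts by 0.25 × 0.27 = 0.07 SD.
- Change from baseline to session 9 is then overstated by 0.27 − 0.07 = about 0.2 SD in that arm. Change from baseline to the later visits is not shifted, because 0.07 − 0.07 = 0.

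Weaker dependence on the score gives smaller shifts. If the same share leaves each arm in the same way, the shifts largely cancel between arms.

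**The case against.** The strongest reply is that the article names a method for missing data before it names the ANOVA, so omission of dropouts does not necessarily follow. The link between the two could be set out in an analysis plan or in the cited method reference, neither of which is at hand. Part of this stands. A reader might infer that the trial will simply run a complete-case analysis, and the document does not establish that, because it also names the mixed model. But nothing in the text says that the ANOVA is run on filled-in data, and a random coefficient model is not ordinarily a means of filling cells. The article states both methods and the promise, and they conflict as written. That is more than an omitted detail.

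Other limits also stand:

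- **The second branch is milder.** A missed visit removes a person from that visit's regression only. A correctly specified baseline-adjusted regression stays valid if missingness depends only on arm and baseline.
- **Dropout related to arm alone** does not bias the comparison between arms. Dependence on earlier scores is what matters. The article neither shows it nor rules it out, and it does include retention measures (free sessions, paid travel, written feedback).
- **Inflating 39 to 45** does not show that dropouts will be excluded. The same allowance is ordinary with mixed models, since missed visits lose information.
- **A serious loss of power** is tempting to infer but is not supported at 15% dropout. Larger losses need a missed-visit rate that the article does not give. If each of the four later visits were missed independently with probability 3%, 5% or 10%, with no other dropout, 45 × (1 − p)⁴ gives about 40, 37 or 30 complete cases. On top of 15% dropout it gives about 34, 31 or 25. These are assumptions, not forecasts.

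**Conclusion.** The point holds as an internal contradiction. The article commits to keeping dropouts and names a model that can do so, yet assigns the results to analyses that, run as stated, leave them out. It does not say which one gives the primary result. At 15% dropout about 7 of 45 participants are affected and about 38 remain in the ANOVA. Power is about 0.80, assuming sphericity and no further missed visits.

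The harm is the broken intention-to-treat promise and a possible bias. In the one-arm extreme worked above, that bias reaches roughly 0.2 SD in the change to session 9 and is absent from the change to later visits. Its actual size cannot be known from the document. The contradiction should be resolved before analysis because it concerns the population and the model for the primary outcome.

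**What to change.** State that the random coefficient (linear mixed) model already named is the primary analysis, in place of the repeated-measures ANOVA. Specify:

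- all randomised participants, in their assigned arm;
- all observed visits, with no deletion of incomplete cases;
- visit as a categorical factor, with group and group-by-visit terms;
- likelihood-based estimation, with the missing-at-random assumption stated.

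A complete-case ANOVA may be kept as a sensitivity analysis and labelled as such. The switch between branches on a baseline significance test then has no role in the primary analysis.

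The cost is a revised analysis text and one sentence noting that the 39 was computed for the ANOVA interaction test. If baseline stays in the model as one of the five visits, the group-by-visit test keeps the same 8 numerator degrees of freedom, so that calculation remains a reasonable guide. If baseline becomes a covariate instead, four outcome visits remain and the justification needs rewording. Inviting those who stop treatment to the later assessments would be a change of conduct and is not part of this correction.

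### A baseline significance test decides which outcome model is used and whether baseline is a covariate, and one branch ends in an unclear Kruskal-Wallis step

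*Protocol article*

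**What the plan says.** All the relevant text is in the second paragraph of Data analysis in the protocol article.

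- **First branch.** The condition is "If there will be no significant difference between various outcome measures in the three groups at baseline". When it is met, the plan for the outcomes is stated like this: "outcome measures will be analyzed using a 3 × 5 repeated measure analysis of variance with group" varying between subjects. The repeated factor is given as "time (baseline, session 9, session 17, post-intervention, follow-up) as within-subject factor". Baseline is one of the five outcome levels here, not a covariate. A Tukey post hoc test follows.
- **Second branch.** The opposite condition is "if a significant difference will be obtained for outcome measures in the three groups at baseline". In that case the plan changes to a different model, worded as "a separate regression analysis will be done by considering group and baseline as covariates at each assessment point". Those visits are session 9, session 17, week 13 and week 25.
- **Closing sentence.** Directly after the second branch: "The differences will be calculated via Kruskal-Wallis". It does not say whether this means raw scores, change scores or a fallback for non-normal data.

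Significance is two-sided at 0.05 throughout. Neither branch is named as primary, and the section fixes no primary visit or contrast. Sample size calculation assumes Cohen's f of 0.25, a correlation of 0.25 among repeated measures, 80% power and 5% alpha. It arrives at 39, raised to 45.

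**The concern.** Allocation is randomised, so a baseline difference between arms is a chance finding and its p-value does not show whether adjustment is needed. What matters is how strongly baseline predicts the later score, and the protocol itself assumes a correlation of 0.25.

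The two branches also answer different questions. One is a single repeated-measures analysis over five visits, giving a group effect and an 8-df group-by-time interaction. The other is four separate visit-level adjusted comparisons. Which of them becomes the trial's result is settled by the data.

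The trigger is loosely worded too. It does not say whether each outcome has its own gate or whether a difference on any scale switches all of them. Finally, Kruskal-Wallis takes no covariate. If the closing sentence means a test of raw or change scores, the branch chosen because baseline differed would end in a test that does not adjust for it.

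**Working it through.** **Inputs.** f = 0.25, correlation ρ = 0.25, N = 39 and 45 (Sample size calculation); 1:1:1 allocation, so 15 per arm at 45 (Trial design); two-sided alpha 0.05 and five time points (Data analysis). Assumptions: normal data, compound symmetry, and ρ = 0.5 and 0.7 as alternatives to the documented 0.25.

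**1. The plan's own figure.** For the group-by-time interaction, λ = f²·N·m/(1 − ρ) = 0.0625 × 39 × 5 / 0.75 = 16.25, with (3 − 1)(5 − 1) = 8 and (39 − 3)(5 − 1) = 144 df. Power is 0.812, and 39 is the smallest balanced N reaching 80%. Then 39 × 1.15 = 44.85, rounded up to 45. The between-groups test would need 65 and the within-subject test 30, so the trial was sized on the interaction, which only the first branch tests.

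**2. What the gate lets through.** The critical F(2, 42) is 3.22. For arms A and C a distance d apart with B midway, F = n·d²/4 in SD units, so the largest non-significant gap is √(4 × 3.22 / 15) = 0.93 SD. By the noncentral F, a gap of 0.5 SD is flagged 20% of the time and 0.8 SD 46%.

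**3. Where such a gap goes.** With no treatment effect, a baseline gap d is expected to leave ρ·d at each later visit. The gap in the five-visit mean is d(1 + 4ρ)/5 and the gap in change from baseline is −(1 − ρ)d. At d = 0.93 and ρ = 0.25 these are 0.93 × 2/5 = 0.37 SD and −0.75 × 0.93 = −0.70 SD. The first bears on the group main effect. The second bears on the change-like interaction and has the opposite sign.

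**4. First branch under the null, baseline p between 0.05 and 0.20** (60,000 simulated trials per correlation, 15 per arm):

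| ρ | Group effect | Interaction | ANCOVA, week 13 |
|---|---|---|---|
| 0.25 | 10.6% | 8.7% | 5.0% |
| 0.5 | 12.8% | 7.2% | 4.7% |
| 0.7 | 12.8% | 6.1% | 5.1% |

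**5. Second branch under the null, given a significant baseline** (about 5% of trials per outcome; week-13 scores; 40,000 or more trials per correlation):

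| ρ | Kruskal-Wallis, raw | Kruskal-Wallis, change | ANCOVA |
|---|---|---|---|
| 0.25 | 6.8% | 19.7% | 4.6% |
| 0.5 | 15.6% | 14.9% | 4.6% |
| 0.7 | 27.1% | 10.0% | 4.9% |

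Only about 5% of 40,000, or 2,000 trials, feed each cell of this table. Repeat runs put the Kruskal-Wallis cells at 6–7%, 15–16% and 27–29% (raw) and 20–22%, 14–15% and 10–11% (change).

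**6. Averaged over all baselines.** The two-stage procedure's type I error at week 13 is about 3% to 6%, depending on the test read in each branch.

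**7. Precision at a single visit.** Adjustment multiplies the residual variance by 1 − ρ²: 0.94 at ρ = 0.25, 0.75 at 0.5 and 0.51 at 0.7.

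**The case against.** The best defence has four parts, and most of it stands as a limit on how far the point goes.

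- **Overall error.** A reader might infer from the tables that the trial's false-positive rate is badly inflated. It is not: the overall figure is about 3% to 6%. The interaction, given any non-significant baseline, rejects about 4% to 5% of the time. The raised rates apply to subsets of trials: about 15% for baseline p of 0.05 to 0.20 and about 5% for a significant baseline. A 0.93 SD gap is the extreme edge of what passes.
- **The interaction is not blind to baseline.** Baseline is a level of time, so the interaction behaves like a comparison of changes. The 0.37 SD carry-over belongs to the group effect, not to the test the trial was sized on. This stands, but the interaction over-corrects when correlation is low, and its conditional error is still above 5%.
- **Kruskal-Wallis.** It is tempting to say that it definitely undoes the adjustment. The sentence is too vague for that. The section elsewhere pairs ANOVA with Kruskal-Wallis and plans normality checks, so a fallback for non-normal data is plausible. That fallback would still drop baseline, and the text does not state it.
- **Power and switching.** With 13 per arm, ρ = 0.25 and a 1.0 SD A–C gap at all later visits, the interaction has about 40% power and adjusted week-13 ANCOVA about 60%. A reader might credit the difference to adjustment. Unadjusted week-13 ANOVA already gives 57% to 59%, so nearly all of it is an 8-df test against a 2-df test. Likewise, 1 − 0.95^16 = 56% as the chance of a switch needs a trigger shared by all scales and 16 independent scales. With outcome-by-outcome gating the primary switches about 5% of the time.

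**Conclusion.** The point holds in a bounded form. The section prints a rule under which a baseline p-value selects the model, the estimand and the use of baseline as a covariate. That is a faulty stated rule, not a detail left to an analysis plan.

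Its cost is conditional bias, a target not fixed in advance and some lost precision. For baseline p of 0.05 to 0.20, null error is about 11% to 13% (group effect) or 6% to 9% (interaction), against about 5% for ANCOVA. Given a significant baseline, Kruskal-Wallis rejects about 6% to 7% (raw) or 20% to 22% (change) at the documented correlation of 0.25. At an assumed 0.7 the figures are 27% to 29% and 10% to 11%. The precision loss at one visit is small at 0.25 and grows with the correlation.

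These figures rest on normality, compound symmetry and 15 complete participants per arm. The documents do not support a claim of large overall alpha inflation, of a large power loss due to non-adjustment alone, or of one certain meaning for the Kruskal-Wallis sentence.

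**What to change.** Delete the baseline test as a gate, both branches and the Kruskal-Wallis sentence. Replace them with one rule for the primary outcome and each quantitative secondary outcome:

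- One linear mixed model on the four post-baseline visits, with group, visit, group × visit, baseline score and baseline × visit, fitted whatever the baseline looks like.
- The primary contrast (which arms, which visit or average of visits) named in advance.
- Baseline-adjusted differences with 95% confidence intervals.
- One pre-named sensitivity analysis for non-normality that keeps baseline, such as rank ANCOVA, reported regardless of the residuals so that no new data-driven choice is introduced.

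The change is to text only. Baseline scores are already collected, and the section already commits to random coefficient analysis for missing data, which belongs to the same family of models.

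There are two costs. The 39 was computed for the interaction test, so the sample-size justification must be restated for the chosen contrast. Trial status expected the last assessments by June 2023, before the article's publication in September 2023, so the change may fall after data collection. It should be dated, recorded as an amendment and fixed before any outcome is analysed by group.

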## Methods

### Trial design

A parallel, three-armed, double-blinded (assessor and patients) randomized controlled trial will be conducted. Individuals will be assigned to each group in a ratio of 1:1:1 (group A: occupation-based interventions with responsibility feedback; group B: occupation-based interventions without responsibility feedback; group C: conventional interventions). The CONSORT diagram [38] will present the trial design (i.e., enrollment, allocation, and assessments) in brief (Fig. 1). This clinical trial follows the recommendations for Interventional Trials (SPIRIT) [39] statements (Additional file 1).

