### Primary outcome measure

The primary outcome of this trial will be participation satisfaction assessed with the Utrecht Scale for Evaluation of Rehabilitation-Participation Satisfaction Scale (USER-P). The satisfaction scale consists of 10 items including vocational activities, leisure activities, and social relationships. Each item will be rated on a 5-point Likert scale. The summation of scores will be converted to a 0–100 scale, with higher scores indicating greater participation satisfaction [54]. The Persian version of the USER scale has shown appropriate validity and reliability [55].

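### The primary analysis fixes no deciding effect or visit, and Tukey on the group factor, as usually run, averages in the pre-randomisation baseline and dilutes the arm differences

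*Protocol article*

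**What the plan says.** The Primary outcome measure section names USER-P participation satisfaction and attaches no visit or group contrast to it.

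The Data analysis section has two branches. If the arms do not differ significantly at baseline, a 3 × 5 repeated-measures ANOVA is used, with group as the between-subject factor and "time (baseline, session 9, session 17, post-intervention, follow-up) as within-subject factor". It is followed by: "A Tukey post hoc test will be performed for multiple comparisons". The text does not say which means Tukey compares, or whether the group effect or the interaction decides.

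If the arms do differ significantly at baseline, the plan switches to separate regressions on group and baseline at each of the four later assessments.

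One rule covers everything: "All analyses will be considered significant with a 2-tailed" P < 0.05.

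The Sample size calculation section gives a "standardized effect size of 0.25, correlation among repeated measures of 0.25, power of 80%, and first type error of 5"%, and then: "The total sample size was calculated as 39 subjects which increased to 45 subjects by assuming a 15% dropout rate". It does not say which ANOVA effect was powered.

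**The concern.** Baseline data are collected before allocation, so the expected difference between arms at that visit is zero. Counting the visit as an outcome level pulls any five-visit group mean difference towards zero. The pairwise comparison that would answer the trial's three-arm question is then both diluted and different from the effect on which the trial appears to have been sized.

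The analysis text also yields several results for the one primary outcome and gives them equal standing at 0.05. A favourable result on any of them could be presented as the primary finding. At stake are a between-arm estimate that is too small, power lost in a 45-patient trial, and a primary conclusion whose false-positive rate exceeds 5%.

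**Working it through.** **Inputs.** From the protocol: Cohen's f = 0.25, correlation ρ = 0.25, power 80%, α = 0.05, N = 39 raised to 45, three arms 1:1:1 (13 or 15 per arm), five visits. Assumed, because the protocol does not give them: an A–C gap of 1 SD at full effect, equal correlation between all visits, a second correlation of 0.6, and the time profiles below.

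**1. Reproducing 39.** Group-by-time interaction, sphericity assumed: λ = f²·N·m/(1 − ρ) = 0.0625 × 39 × 5/0.75 = 16.25, with (3 − 1)(5 − 1) = 8 and (39 − 3) × 4 = 144 df. Power is 0.812, and 39 is the smallest balanced N that reaches 80%. Then 39 × 1.15 = 44.85, giving 45. With the same inputs the group effect needs 66 and the time effect 30, so among the three effects of the 3 × 5 model only the interaction gives 39.

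**2. Power of the group effect, which Tukey follows.** λ = f²·N·m/(1 + (m − 1)ρ) = 0.0625 × 39 × 5/2 = 6.09, with 2 and 36 df: power 0.553. At N = 45, λ = 7.03: power 0.624. This uses the same f for a different effect.

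**3. Dilution of the five-visit mean, relative to the week-13 difference.**
- Constant (0, 1, 1, 1, 1): 4/5 = 0.80
- Building (0, 0.33, 0.67, 1, 1): 3/5 = 0.60
- Building, half lost by week 25 (0, 0.33, 0.67, 1, 0.5): 2.5/5 = 0.50
- Present only at weeks 13 and 25 (0, 0, 0, 1, 1): 2/5 = 0.40

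**4. Pairwise power, 13 per arm, Tukey critical value 2.444 on 36 df.** Noncentrality = difference/√(2v/13), where v is the variance in SD² units:
- five-visit mean: v = (1 + 4ρ)/5, which is 0.400 at ρ = 0.25 and 0.680 at 0.6
- baseline-adjusted mean of four visits: v = (1 + 3ρ)/4 − ρ², which is 0.375 and 0.340
- baseline-adjusted week 13: v = 1 − ρ², which is 0.9375 and 0.640

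The four-visit mean keeps 1 of a constant effect and 3/4 of the building one. Example at ρ = 0.25, constant: 0.8/√(0.8/13) = 3.22 for the five-visit mean, against 1/√(0.75/13) = 4.16 for the four-visit mean.

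| ρ | Profile | Five-visit mean | Adjusted four-visit mean | Adjusted week 13 |
|---|---|---|---|---|
| 0.25 | constant | 78% | 95% | 58% |
| 0.25 | building | 50% | 75% | 58% |
| 0.6 | constant | 52% | 97% | 77% |
| 0.6 | building | 29% | 79% | 77% |

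These figures ignore the one degree of freedom spent on the covariate and the small variance cost of chance baseline imbalance.

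With no difference at baseline, the four-visit mean is always 5/4 of the five-visit mean. Its noncentrality is therefore larger by 1.25 × √(0.400/0.375) = 1.29 at ρ = 0.25 and by 1.25 × √(0.680/0.340) = 1.77 at 0.6. This holds for any profile and any size of gap.

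**5. False positives on one outcome, no true effect, 15 per arm (simulated).** Group effect or interaction below 0.05: about 10% (two independent tests would give 1 − 0.95² = 9.75%). Any of the four baseline-adjusted visit regressions: about 16–19% (four independent tests would give 1 − 0.95⁴ = 18.5%).

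**The case against.** The strongest reply is that the plan can be read more kindly. It does not say that Tukey compares five-visit means; comparisons at each visit would also fit the words and would not be diluted. The sizing points to the interaction as the intended test, and baseline is a legitimate level there because the interaction measures divergence from it. Tukey already controls error across the three pairwise comparisons. An article may also leave post hoc detail to a fuller plan.

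Much of this stands. The five-visit reading is an inference from standard practice with a between-subject factor. The interaction is not diluted. The fallback regressions adjust for baseline, so they are not diluted either. That branch opens only after a significant baseline difference, in about 5% of randomised trials for a single outcome.

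It does not remove the point. The interaction is never named as decisive, and as an 8-df omnibus test it does not say which arm is better. If Tukey was meant visit by visit, no visit is named, and its control over three pairs does not extend across visits. The 0.05 rule for all analyses is written in the protocol, so this is more than detail left for later.

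A second reply is that choosing week 13 would be the reviewer's preference and could lose power. That is correct at the planning correlation under a constant effect (58% against 78%), which is why week 13 alone is not the recommended choice.

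**Conclusion.** The concern holds in this form: the protocol names no deciding effect, contrast or visit for USER-P satisfaction, and its pairwise procedure, as usually run, averages in a visit at which no difference can be expected. The estimate then keeps 80% of a constant effect and 60% or less of one that builds and then holds, wanes or appears late. The trial is sized on the interaction (81% power at 39), while the group effect has 55% at 39 and 62% at 45.

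A reader might infer more than the documents support:
- that every effect shrinks by a fixed 20% to 40%: the protocol gives no time profile, and the profiles above run from 20% to 60%;
- that the whole analysis is diluted: the interaction and the fallback regressions are not;
- that the primary false-positive rate is 16–19%: that figure applies only within the fallback branch, and the main branch gives about 10%, if either effect is accepted as success.

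The power figures rest on the assumed 1 SD gap, equal correlations and complete data on 13 per arm. A different gap changes their level but not the advantage of the adjusted four-visit mean over the five-visit mean.

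**What to change.** In all cases, and not only after a significant baseline test, take baseline out of the outcome vector and use it as a covariate. Name one decisive result for USER-P satisfaction: Tukey-adjusted pairwise differences between arms in the baseline-adjusted mean of the four post-baseline visits. Report single visits, the group-by-time interaction and all secondary scales as supportive, with 95% confidence intervals.

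The change is to the analysis wording only; no new patients or data are needed. The sponsor gives up the option of claiming success on another effect or visit, and the estimate becomes an average over follow-up, which is smaller than the week-13 difference if the effect builds.

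If week 13 alone is preferred, the cost should be stated: about 58% power at correlation 0.25, below the current plan under a constant effect (78%), though above it if the effect builds (50%) or at correlation 0.6 (77% against 52% or 29%). The choice depends on the expected profile. If the effect appears only at weeks 13 and 25, the four-visit mean keeps half of it: noncentrality 0.5/√(0.75/13) = 2.08, about 37% power, against 58% for week 13.

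### Single-step Tukey for the three arm comparisons is valid but inefficient: a closed step-down version keeps the same 5% family-wise error and rejects at least as much, for a modest gain on A versus B.

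*Protocol article*

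**What the plan says.** The trial has three arms: occupation-based treatment with responsibility feedback (A), the same without feedback (B), and conventional treatment (C). Under Trial design, "Individuals will be assigned to each group in a ratio of 1:1:1". Under Sample size calculation, "The total sample size was calculated as 39 subjects which increased to 45 subjects by assuming a 15% dropout rate", which is 13 per arm evaluable and 15 per arm enrolled. The planning inputs there are "Cohen’s *f* standardized effect size of 0.25, correlation among repeated measures of 0.25, power of 80%, and first type error of 5"%.

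Under Data analysis, when the arms do not differ significantly at baseline, "outcome measures will be analyzed using a 3 × 5 repeated measure analysis of variance with group" and time as factors. The pairwise step that follows is: "A Tukey post hoc test will be performed for multiple comparisons". The level is "All analyses will be considered significant with a 2-tailed *P* < 0.05". No stepwise or closed procedure is named and no pair is singled out as primary. Tukey is attached only to this ANOVA branch. The alternative regression branch, used when baseline differs, states no pairwise adjustment.

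**The concern.** Tukey's single-step test protects against all three pairwise nulls being true, and it applies that protection to every pair whatever the other pairs show. With three arms this is more than is needed. If any two of A = B, A = C and B = C are true, the third is true as well. The only situation with more than one true null is therefore the complete null. Once the complete null has been rejected at 5%, at most one true null is left, and it can be tested at the full 5%.

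A versus B isolates the responsibility feedback, the component that the Background says earlier trials did not consider. Both arms share the occupation-based programme and the 15 minutes of conventional treatment, so this could be the smaller difference, and a smaller difference is what an unneeded threshold costs most. With 13 to 15 patients per arm there is little power to spare.

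**Working it through.** **Inputs.** From the article: three arms at 1:1:1, 39 evaluable and 45 enrolled, two-sided 5%, f = 0.25, correlation 0.25, five assessments. The article gives no pairwise differences, so patterns of arm means are assumed and varied below.

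**The plan's own figure.** Treat 39 as the group-by-time interaction test with sphericity. Then λ = f²·N·m/(1 − ρ) = 0.0625 × 39 × 5/0.75 = 16.25, with df 8 and (39 − 3) × 4 = 144, and power is 81.2%. The next lower multiple of three, N = 36, gives 77.1%. So 39 reproduces, but as a test of the interaction and not of any pair of arms.

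**Critical values.** Tukey: q(0.95; 3, df)/√2 for every pair. Step-down: the same value for the largest |t|; if it is passed, t(0.975; df) for the other two.

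| Per arm | df | Tukey, all pairs | Step-down, other two pairs |
|---|---|---|---|
| 13 | 36 | 2.444 | 2.028 |
| 15 | 42 | 2.429 | 2.018 |

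**Dominance.** Any pair that Tukey rejects exceeds 2.43 or 2.44. The largest |t| then also exceeds it, so the gate is open, and the pair exceeds 2.02 or 2.03 as well. Step-down therefore rejects it too. This needs no assumption about effects.

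**Family-wise error (simulated).** Under the complete null both procedures are at about 5.0%. With A = B and C far away, Tukey uses 2.0% and step-down 5.0%.

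**Scale of the effects.** With equal steps d (A > B > C), f = d·√(2/3), so f = 0.25 means d = 0.306 SD. With A above B = C by d, f = d·√2/3, so f = 0.25 means d = 0.530 SD.

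**Power for A versus B, Tukey to step-down** (at least 300,000 simulated trials per case; repeat runs differ by about 0.1 to 0.2 points).

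*f = 0.25 on a single contrast with SD 1:*
- 15 per arm: equal steps 6.5% to 9.7%; A > B = C 17.7% to 20.9%.
- 13 per arm: equal steps 5.8% to 8.6%; A > B = C 15.1% to 17.8%.

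*f = 0.25 on the five-visit average.* The SD of the average is √((1 + 4 × 0.25)/5) = 0.632 of the single-visit SD:

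| Pattern | 13 per arm | 15 per arm |
|---|---|---|
| Equal steps | 12.7% to 19.9% | 14.6% to 22.9% |
| A > B = C | 38.9% to 45.0% | 45.6% to 52.3% |
| A–B gap twice B–C | 21.7% to 30.2% | 25.6% to 35.2% |
| B–C gap twice A–B | 6.0% to 11.0% | 6.8% to 12.5% |

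The gains run from 5.0 to 9.6 points.

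*Larger effects, single contrast, 15 per arm:*
- Steps of 0.6 SD (f = 0.6 × 0.816 = 0.49): 22.7% to 34.9%.
- Steps of 0.7 SD (f = 0.57): 31.6% to 46.0%.
- A = 1 SD with B = C (f = 0.47): 62.4% to 69.6%.

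**When A–B is the largest difference.** With A = 1, C = 0.5 and B = 0 (15 per arm), power moves only from 62.4% to 64.2%.

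**Unequal arms.** The gate must be the largest |t|, not the largest raw difference, because after dropout the two need not be the same pair. With A = 0.8 SD and B = C = 0, a gate on the raw difference misses a pair that Tukey-Kramer rejects in about 1% of trials at 15/15/9 and 0.1% at 15/13/11. Gated on |t|, this never occurs.

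**The case against.** The strongest reply is that nothing here is wrong. Tukey is a standard choice, it controls family-wise error over all three pairs, and its simultaneous intervals agree with its tests. Step-down gives up that agreement for power, which is a matter of preference. This stands, and it limits the point to an efficiency improvement.

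The size is also easily overstated. A reader might infer gains of 7 to 14 points for this trial. On a single contrast those belong to f of about 0.47 to 0.57, roughly twice the 0.25 the article plans on.

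A reader might also take A versus B to be the primary or the smallest contrast. The documents name no primary pair and give no pairwise differences. The shared treatment content makes a small A–B difference plausible, but that is conjecture, and where A–B is the largest difference the gain nearly vanishes.

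The article does not say which means Tukey compares (a single visit or the average over visits), so none of these powers belongs to a fully defined test in the plan. That is why two scales are shown; the dominance argument holds on either.

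Lastly, timing. The Trial status section expected the last assessments by June 2023 and the article appeared in September 2023. Moving to a less strict rule at that stage needs a dated record, so the cost is more than rewording.

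**Conclusion.** The point holds as a cheap improvement, not as an error. That a step-down procedure gated on the largest |t| keeps 5% family-wise error and rejects everything Tukey rejects is a matter of logic with three arms, and the simulations agree. The benefit for A versus B is modest: about 3 percentage points at the planned f = 0.25 on a single contrast, and about 5 to 10 points if that f applies to the five-visit average with correlation 0.25. It is 7 to 14 points on a single contrast only at about twice the planned effect. All of these rest on assumed patterns of arm means, normal data and a common SD.

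Two stronger readings are not supported. The documents do not show that the planned Tukey analysis is invalid. Nor would the change rescue the comparison: at f = 0.25, A versus B stays at or below about 52% power in every pattern tried, and below 10% in the least favourable single-contrast cases.

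**What to change.** Replace the Tukey sentence with:

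> The pair with the largest absolute t statistic is compared with the Tukey (Tukey-Kramer if arms are unequal) critical value at 5%; if significant, each of the other two pairs is tested at two-sided 5%; if not, no pair is declared different. Tukey simultaneous confidence intervals are reported alongside as descriptive output.

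This needs no extra patients or data and can be worked out from ordinary pairwise output. It must be dated and documented before outcome data are compared by arm, through the registry route that the Trial status section gives for protocol modifications. If arm comparisons have already been seen, plain Tukey should stay. The remaining cost is that a reported Tukey interval may include zero for a pair that the step-down rule declares different, and the report should say so.
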